#### Data analyses of primary outcomes

For analysis of the primary (HPV vaccination initiation) and secondary endpoints (HPV vaccination completion), the uptake rate of HPV vaccination pre- and post-intervention will be estimated separately with a 95% exact confidence interval using all eligible cases from both phases. The one-sample binomial exact test will be used to test whether the rate after the intervention is higher than the baseline rate (P0 = 13.5%). We will also perform the Chi-square test to compare the rate change between control and interventional phases, which will be exploratory. Logistic regression will be used to further adjust background difference in study population in pre- and post- intervention phases. For the longitudinal data collected from the intervention phase, the data structure holds multi-level information from patients, providers, and clinic levels. The goal of the analyses is to identify the factors that might impact HPV uptake from each level of information, which might lead to the future improvement of implementation strategy. Data will be described using summary statistics (e.g., quartiles, median, mean, standard deviation) for continuous variables and marginal distribution (frequency and percentage) for categorical variables. The univariate association with the HPV vaccination (yes vs. no) will be tested in logistic regression for each variable separately. The change of survey response between baseline and a follow-up time point will be tested by paired tests (e.g., paired t-test, McNemar test). Along with data visualization, all above mentioned descriptive and univariate association analyses will be repeated within each of the three clinics. Data will be pooled to build the multilevel analysis models, we mainly consider using the mixed-effect model and/or Bayesian multilevel modeling, in which the random effect will be considered at provider and clinical levels. We will follow the key modeling considerations listed by J.J. Hox [29] to identify the significant mediators and moderators at different levels that impact the uptake of HPV vaccination.

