## Background

HPV-related anal cancer occurs in excess rates among people living with HIV (PLWH) [1], and has been increasing in incidence [1]. Notably, the incidence of anal cancer among men who have sex with men (MSM) is 20- to 40- fold greater relative to non-MSMs [2]. The Human Papillomavirus (HPV) is responsible for 90% of anal cancers where oncogenic HPV type 16 is responsible for 90% of anal cancers [3]. It is presumed the increased risk for anal cancer among PLWH is due to an impaired ability to clear HPV infections and increased reactivation of latent HPV infection. Of note, highly active antiretroviral therapy (HAART) has modest to no effect on HPV clearance or persistence; thus, other mechanisms may be involved that result in cellular immune dysfunction [4].

The safety and efficacy of the HPV vaccine has been evaluated in PLWH and is shown to be safe and highly immunogenic against oncogenic HPV types 16 and 18 [5–8]. The HPV vaccine also has been shown to decrease the risk of HPV-related anal intraepithelial neoplasia in a sample of MSMs [9]. Thus, anal cancer can be potentially a preventable disease through the use of the HPV vaccine [3]. However, very limited research has been conducted on the uptake of HPV vaccination among PLWH. One study found among a sample of young MSM’s who self-reported as HIV-positive, HPV vaccine initiation was 13.4% [10]. Although uptake is low, studies of the acceptability of the HPV vaccine has been found to be high among high risk groups like MSMs [11–13].

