The Advancing HPV vaccination for HIV Positive Adults (CHAMPS) study seeks to expand the success of the 4 Pillars™ Program and tailor, refine, and implement in the HIV positive population, who are at high risk for HPV-related cancers and can obtain the most benefit from the vaccine. The strategies selected from the 4 Pillars™ Program are based on an extensive review of the HIV and related literature (Table 2) [21–28]. The intervention will be implemented in three HIV community clinics in Georgia, USA and enroll *n* = 365 PLWH, age 18–45 years, from those clinics. Guided by the RE-AIM framework, the proposed specific aims are:Tailor and refine the 4 Pillars™ program for implementation in three HIV community clinics in Georgia.Test the effectiveness of the 4 Pillars™ program as measured by an increase in uptake rate in initiation of the HPV vaccine (primary outcome) and vaccine completion (secondary outcome) compared to historical baseline vaccination rate (control) among PLWH. It is hypothesized after implementation of the 4 Pillars™ program, we estimate an uptake rate of > = 13.5% in initiation of HPV vaccination.Identify mediators and potential moderators (HPV knowledge and awareness and vaccine hesitancy) of the intervention effects on HPV vaccination.Assess the sustainability of the intervention in vaccine uptake post-intervention and assess scalability of the program for wider implementation via a future national randomized control trial.

**Table 2 Tab2:** Overview of selected intervention strategies guided by the 4 Pillars™ Program

Pillar Strategy	Level	Intervention Component
Pillar 1: Convenience	Provider-	• Incorporate recommendation of the HPV vaccine with each clinic visit. • Perform HPV vaccination on-site
Pillar 2: Communication and education	Patient-	• Provide patient education on risk of HPV-related cancer and benefit of HPV vaccination
Pillar 3: Enhanced systems	Clinic-	• Provider and staff education on HPV vaccination via an in-service training • Document vaccination in EMR system
Pillar 4: Motivation	Clinic- Provider- Patient-	• Clinic designated Immunization Champion to provide coaching and motivation of regularly tracked vaccination progress • Provide patient check-in, reminders, and motivation for HPV vaccine completion • Communicate vaccination reminders by text, phone, and social media messaging

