### Data analysis plan

#### Study outcomes

Initiation of the HPV vaccine is the primary outcome endpoint (Fig. 2). Initiation of the HPV vaccine is defined as receiving the first or second immunization from the series. This variable will be measured by electronic medical records and GRITS at baseline (historical control) and 24 months post baseline. We hypothesize the initiation rate will be higher than the historical control rate. Completion of the HPV vaccine is the secondary outcome variable. Completion is defined as receiving all three immunizations from the series, regardless of time. This variable will be measured by electronic medical records and GRITS baseline (control) and 24 months post baseline.

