#### Statistical power

Based on our preliminary data, we found that HPV vaccination rate is around 13.5% (P0) in general, and another larger study in the literature found a very similar rate of 13.6% [10]. We powered the study to detect an uptake rate > 13.5% after the intervention. Thus, a sample size of 317 achieves 80% power to detect a superiority difference of 5% (PB-P0) using an exact one-sided test with a significance level (alpha) of 0.05. We anticipate a 5% superiority difference is reasonable to achieve with an uptake rate of 18.5% (PB) after the intervention. We will be able to reject the Null hypothesis and claim the uptake rate of > 13.5% after 54 patients have initiated the HPV test. After taking about 15% of the drop-off rate into account, we plan to include 365 participants among 3 clinics for the intervention phase. The calculation was by PASS 2020 for testing superiority of one proportion using the Exact test. The Null hypothesis is *P* < = 13.5% and the alternative hypothesis is *P* > 13.5%. For the control phase, we will query all eligible subjects from EMR database among the 3 clinics at 18 months pre-intervention, which could be approximately 2300 subjects [30]. Assuming we end up with the same number of subjects in both control (*N* = 317) and intervention phase (*N* = 317), we will have 81% statistical power to detect an HPV uptake rate difference of 9% (22.5% vs. 13.5%) by two-sided Fishers’ Exact Test and under significance level of 0.05. We anticipate such a difference would be feasible based on our best knowledge and the literature. Regarding the patient- level component of the intervention, all incoming eligible patients will be influenced, and hence 365 participants are the minimum number to capture the follow-up information, the actual number of sample size used for the calculation of HPV vaccination rate will be larger as the vaccination status will be captured automatically in EMR without a consent.

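### The one-sample test gives completion no null of its own: as written it inherits P0 = 13.5%, an initiation rate, and has low power unless nearly all initiators finish the series

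*Protocol article*

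**What the plan says.** The analysis paragraph in Data analyses of primary outcomes opens with both endpoints: "For analysis of the primary (HPV vaccination initiation) and secondary endpoints (HPV vaccination completion". It plans exact 95% intervals for the rate before and after the intervention. The next sentence gives the only formal test: "one-sample binomial exact test will be used to test whether the rate after the intervention is higher than the baseline rate (P0 = 13.5" per cent. No other null value, target or power for completion appears in the article.

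On where 13.5% comes from:
- Statistical power: "Based on our preliminary data, we found that HPV vaccination rate is around 13.5% (P0) in general". This wording does not name the endpoint. The same section supports the figure with reference 10 and states the rejection rule as 54 patients who have initiated.
- Background, on reference 10: "HPV vaccine initiation was 13.4% [10".
- The second specific aim, also in Background: "we estimate an uptake rate of > = 13.5% in initiation of HPV vaccination".

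On completion, Study outcomes says: "Completion is defined as receiving all three immunizations from the series, regardless of time". The Abstract, the specific aims and Study outcomes all describe completion as compared with a historical baseline (control).

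**The concern.** A one-sample test is only as good as its null value. For initiation, 13.5% is the rate the trial was designed around. Completion is a stricter endpoint: everyone with three doses has had a first dose, so the historical completion rate cannot exceed the share who ever started. Tested against 13.5%, completion is asked whether more patients now finish the series than used to start it. That is not the question in the aims.

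The formal completion result could therefore fail to reject after a real improvement, because the bar was set for another endpoint.

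**Working it through.** **Inputs.** From Statistical power: P0 = 13.5%, planned rate 18.5%, n = 317, exact one-sided test at 0.05, rejection at 54, stated power 80%. From Study outcomes: completion means all three doses. Assumed, because the article does not give it: f, the share of initiators who complete. Initiation is taken as at least one dose.

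**1. The plan's own figures.** The smallest count c with P(X ≥ c | 317, 0.135) ≤ 0.05 is c = 54. The attained alpha is 0.0425 at 54 and 0.0585 at 53, so the stated count reproduces. Exact power is P(X ≥ 54 | 317, 0.185) = 77.0%. The stated n and 80% match the normal-approximation formula (n = 316.05, rounded up to 317; power 80.1%). The 3-point gap is a side matter and does not change this point.

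**2. What rejection requires for completion.**
- 54/317 = 17.0% of patients must complete.
- At 18.5% initiation: 0.1703/0.185 = 0.92, so 92% of the expected initiators must complete.
- 0.135/0.185 = 0.73. If fewer than 73% complete, true completion is below 13.5%. The null is then true, however far completion rose from its own baseline.

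**3. Power by share completing.** Power against 13.5% is P(X ≥ 54 | 317, 0.185f). For comparison, let baseline and target completion be the same share f of 13.5% and 18.5%, and test exactly, one-sided at 0.05, against completion's own baseline.

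| f | Completion, baseline to target | Power against 13.5% | Own-baseline rejection count | Power against own baseline |
|---|---|---|---|---|
| 0.50 | 6.75% to 9.25% | 0.001% | 30 | 47.6% |
| 0.60 | 8.1% to 11.1% | 0.1% | 35 | 54.0% |
| 0.70 | 9.45% to 12.95% | 2.2% | 40 | 59.5% |
| 0.75 | 10.1% to 13.9% | 6.4% | 42 | 65.1% |
| 0.80 | 10.8% to 14.8% | 14.9% | 45 | 64.3% |
| 0.87 | 11.7% to 16.1% | 34.7% | 48 | 70.0% |
| 0.90 | 12.15% to 16.65% | 45.0% | 49 | 73.7% |
| 1.00 | 13.5% to 18.5% | 77.0% | 54 | 77.0% |

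The 0.87 row is there because the only completion effect in the article, from an adolescent trial cited in Background, is a gain of 14.8 points against 17.1 for initiation (14.8/17.1 = 0.87). That is a ratio of gains in another population, not a completing share, so it is only a reference value.

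**4. Sensitivity.**
- Higher initiation: at 22.5% (the rate in the article's two-sample power statement) and n = 317, power against 13.5% is 4.2% at f = 0.6, 29% at 0.7 and 69% at 0.8.
- Larger set: Statistical power says the number used for the rate will exceed 365 but does not give it. Assuming 2300, borrowed from the control query, rejection is at 339. Power is 0.6% at f = 0.7, 12% at 0.75, 54% at 0.8 and 97% at 0.87. A larger set helps only if more than about 73% complete; below that it makes rejection less likely.

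**The case against.** **The test may be meant for initiation only.** The test sentence is in the singular, the section heading refers to primary outcomes, and P0 is tied to initiation elsewhere. This reading is possible. But the paragraph's opening names both endpoints, and on the narrower reading completion has no stated formal test. The same clarification is needed either way.

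**Other planned analyses would reveal a rise.** This stands. The same section plans exact intervals before and after, an exploratory Chi-square test between phases and adjusted logistic regression. Process evaluation adds a demographically adjusted percent change in completion from the control phase. A reader might infer that a genuine rise would end up as a wrong negative conclusion for the trial. The documents do not support that: only the formal one-sample result is affected.

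**The loss of power depends on an unknown share.** This also stands. A reader might infer that the completion test has almost no chance of rejecting. That is fair if about 75% of initiators or fewer complete, but not at 87% or 90%, nor with higher initiation or a large EMR set at a high share. Nor should the gain from the fix be shown with a convenient example. A rise from 6% to 11.1% with 365 patients gives 96% power against its own baseline and 0.1% against 13.5%, but it assumes the completing share rises from 44% (6/13.5) to 60% (11.1/18.5). At a constant 60% and n = 317, own-baseline power is 54%.

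**Completers may not be a subset.** Study outcomes defines initiation by the first or second dose, which read literally could exclude people with three. The argument here takes initiation as at least one dose, the natural reading for a rate of starting the series.

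**Conclusion.** The point holds as a should-fix. As written, the paragraph applies an initiation null to completion, which is too high and does not match the article's own aim for that endpoint. At n = 317 and 18.5% initiation, power is low unless nearly all initiators complete, and it cannot exceed the 77.0% available for initiation.

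The size rests on three assumptions: the test sentence covers completion, initiation means at least one dose, and the completing share lies in the range shown. The own-baseline column also treats the historical completion rate as a known constant and the share as unchanged by the programme.

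The primary test is untouched. Because the null is too high, the error makes a false claim of success on completion less likely, not more.

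**What to change.** In Data analyses of primary outcomes, state that P0 = 13.5% applies to initiation only. For completion, name as the test the comparison with the historical completion rate from the EMR/GRITS control query, using the same look-back window and denominator in both phases. The two-sample comparison already planned is preferable to a one-sample test, because it carries the sampling error of the control rate; it would then no longer be only exploratory for completion.

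The cost is about one sentence and no new data, since the control query already covers completion. No power claim for completion is needed, but an expected completion rate would let readers judge what the test can show.

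### The univariate logistic tests carry no clustering term, so any provider- or clinic-level variable tested this way gets a p-value that is too small when uptake clusters

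*Protocol article*

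**What the plan says.** All of this stands in one paragraph of the protocol article, under Data analyses of primary outcomes.

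- On the intervention-phase data: "the data structure holds multi-level information from patients, providers, and clinic levels".
- On the purpose: "The goal of the analyses is to identify the factors that might impact HPV uptake from each level of information".
- On the first inferential step: "The univariate association with the HPV vaccination (yes vs. no) will be tested in logistic regression for each variable separately". No random effect, robust standard error or other allowance for clustering is attached to it.
- On repetition: "all above mentioned descriptive and univariate association analyses will be repeated within each of the three clinics".
- On the later step: the data are pooled into mixed-effect and/or Bayesian multilevel models, "in which the random effect will be considered at provider and clinical levels". This modelling is used "to identify the significant mediators and moderators at different levels that impact the uptake of HPV vaccination".

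Under Statistical power: "we plan to include 365 participants among 3 clinics for the intervention phase". The analysable number there is 317 and the expected uptake is 18.5%. No number of providers and no ICC is given anywhere.

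**The concern.** The univariate rule covers every variable and exempts no level. The article also describes data above patient level: readiness and confidence of clinic staff (Pre-implementation approach), in-service training and three-monthly staff evaluations (Clinic-level intervention approach), and attendance (Process evaluation). If such an attribute is entered as a predictor of a patient's vaccination, all patients of one provider share its value. Ordinary logistic regression counts each of them as an independent replicate, although the replication for that attribute is the number of providers, or three for a clinic attribute.

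If uptake varies between providers for any other reason, the standard error is too small and chance differences between providers reach nominal significance too often. At stake is the reading of these preliminary p-values, pooled and within clinic, in a set of analyses that is meant to inform later implementation strategy.

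**Working it through.** **Inputs from the article.** Analysable N = 317; enrolled N = 365; three clinics; uptake 18.5% after the intervention (all in Statistical power).

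**Inputs assumed.** Number of providers J from 6 to 30; ICC from 0.01 to 0.10; equal panels; a two-valued factor with no true effect.

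**The plan's own figure.** The article gives no figure for the univariate tests. Its N = 317 reproduces from the one-sample formula with P0 = 0.135 and PB = 0.185:

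n = [(1.645·√(0.135·0.865) + 0.842·√(0.185·0.815)) / 0.05]² = 316.05, rounded up to 317.

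This is a normal approximation. The exact power of the stated 54-patient rule at 317 is 77.0%, which is a separate matter. Here 317 serves only as the number of patients.

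**Formula.** With m = N/J patients per cluster, the design effect is DE = 1 + (m − 1)·ICC. The true two-sided error of a patient-level test at nominal 5% is 2·[1 − Φ(1.96/√DE)].

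**Worked cases, N = 317.**

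- J = 6, ICC 0.05: m = 52.8; DE = 1 + 51.8·0.05 = 3.59; 1.96/√3.59 = 1.03; error 30.1%.
- J = 30, ICC 0.05: m = 10.6; DE = 1 + 9.6·0.05 = 1.48; 1.96/√1.48 = 1.61; error 10.7%.
- Clinic factor, 3 clusters, ICC 0.01: m = 105.7; DE = 1 + 104.7·0.01 = 2.05; 1.96/√2.05 = 1.37; error 17.1%.

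**Full range, N = 317.** Each cell gives the formula, then a beta-binomial simulation with 40,000 runs.

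| Clusters | ICC 0.01 | ICC 0.02 | ICC 0.05 | ICC 0.10 |
|---|---|---|---|---|
| 3 (clinics) | 17.1% / 16.5% | 26.5% / 26.2% | 43.2% / 43.0% | 56.3% / 55.7% |
| 6 providers | 11.2% / 11.1% | 17.0% / 16.7% | 30.1% / 30.1% | 43.1% / 43.1% |
| 10 providers | 8.6% / 8.6% | 12.3% / 11.9% | 21.8% / 21.8% | 33.1% / 33.4% |
| 20 providers | 6.7% / 6.6% | 8.5% / 8.5% | 13.8% / 13.4% | 21.4% / 21.4% |
| 30 providers | 6.1% / 5.9% | 7.3% / 6.9% | 10.7% / 10.5% | 16.1% / 15.7% |

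**With all 365 patients.** The largest provider case (J = 6, ICC 0.10) is 45.8% by formula and 47% in a separate simulation with 4,000 runs. The clinic case at ICC 0.10 is 58.8% by formula and 59% by simulation. These set the upper ends of the ranges quoted.

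**Checks.** With ICC = 0 the simulated error of the patient-level test is 4.6% to 5.0%, so clustering causes the excess. A t-test on provider-level rates stays between 4.6% and 5.3% in every scenario with 6 to 30 providers.

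**Within-clinic repeats.** DE depends only on m and ICC. Splitting by clinic leaves the panel size unchanged (6 providers become 2 per clinic, still 52.8 patients each), so at a given ICC the inflation remains. A two-group provider-level comparison has J/3 − 2 degrees of freedom per clinic if providers are spread evenly: 8 for J = 30 and 0 for J = 6.

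**The case against.** The strongest reply is that the plan already recognises the hierarchy. The same paragraph gives the naming of significant factors to pooled multilevel models with provider and clinic random effects, and it groups the univariate tests with the descriptive work. That stands. A reader might infer that false provider or clinic factors will be declared the drivers of uptake and carried into scale-up and a national trial. The article does not support this. It neither presents the univariate tests as the conclusion nor makes them a screen for the multilevel model. The Secondary aims section bases scalability on summaries of evaluation surveys and on a focus group.

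The reply also stands on these points:

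- A reader might infer that errors far above 5% are certain. For provider factors they are not: with 30 providers and ICC 0.01 the error is about 6%.
- The mediators and moderators named in the aims, HPV knowledge and awareness and vaccine hesitancy, are patient-level, and this inflation does not apply to them to the same degree. The article does not say outright that staff attributes will be linked to patients.
- A clinic attribute is constant within a clinic, so it drops out of a within-clinic repeat and produces no false positive there.

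The suggestion that this is detail for a statistical analysis plan does not stand. The article states which test will be used, for each variable, straight after saying that factors are sought at all three levels. Nor does the multilevel model repair the tests in question. It is fitted to pooled data, so no clustered counterpart is stated for the within-clinic repeats, and the pooled univariate p-values stay as they are. With three clinics, a clinic random effect rests on almost no information.

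**Conclusion.** The point holds in a limited form. As written, the univariate step is anti-conservative for any provider- or clinic-level variable entered in it whenever the ICC is above 0. The true error of a nominal 5% test is about 6% to 47% for a provider factor and about 17% to 59% for a clinic factor. These figures rest on an assumed 6 to 30 providers (three clusters for the clinic factor), ICC 0.01 to 0.10, equal panels and 317 to 365 patients; the provider number and the ICC are not in the documents.

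The defect is confined to preliminary p-values, pooled and within clinic. The pooled multilevel model covers provider clustering in the step that identifies factors, but covers clinic-level factors only weakly. The tests of vaccination initiation and completion are separate analyses and are not in question here, and neither are the scalability conclusions.

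**What to change.** Amend the univariate sentence under Data analyses of primary outcomes along these lines:

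- Patient-level variables: univariate logistic regression, as planned.
- Provider-level variables: a univariate logistic model with the provider random intercept already planned for the multilevel step, or an analysis of provider-level rates with small-sample degrees of freedom. Apply this to the pooled data and to the within-clinic repeats. Where a clinic has too few providers for a test, give estimates only.
- Clinic-level variables: description across the three clinics, without p-values, and none in the within-clinic repeats.

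This changes analysis wording only. It needs no new data, because the multilevel model already requires the provider identifier. The downside is wider intervals and fewer nominally significant provider factors; with few providers per clinic, some within-clinic provider comparisons will become descriptive.

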### Clinic selection and patient eligibility

Three HIV community clinics for this study were selected due to agreement to participate in the study, granted study access to electronic medical records, and willingness to make office changes to increase vaccination rates. Patients will be recruited from these three clinics and enrolled in the study based on the following eligibility criteria: 1) HIV positive; 2) 18–45 years of age; 3) understand English; 4) capable of informed consent; 5) have not received or completed the three dose HPV vaccine; 6) no contraindications to receiving the HPV vaccine (i.e., history of an anaphylactic allergy to latex, an immediate hypersensitivity to yeast, current moderate or severe acute illness, and/or are currently pregnant).

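### Three clinics are too few for a reliable random clinic effect or for significance claims about clinic-level moderators; clinic should be a fixed effect (minor)

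*Protocol article*

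**What the plan says.** The section on data analyses of primary outcomes describes the intervention-phase data as hierarchical: "the data structure holds multi-level information from patients, providers, and clinic levels". The stated goal is to "identify the factors that might impact HPV uptake from each level of information". The data are to be pooled into a mixed-effect and/or Bayesian multilevel model, "in which the random effect will be considered at provider and clinical levels", and the models are to be used "to identify the significant mediators and moderators at different levels that impact the uptake of HPV vaccination". In context, the clinical level means the clinic.

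The number of clinics is fixed. The section on statistical power states: "we plan to include 365 participants among 3 clinics for the intervention phase". The section on clinic selection and patient eligibility explains how they were chosen: "Three HIV community clinics for this study were selected due to agreement to participate in the study".

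The third specific aim, in the Background, names the variables of main interest: "Identify mediators and potential moderators (HPV knowledge and awareness and vaccine hesitancy) of the intervention effects on HPV vaccination". These are collected from patients by questionnaire. The primary analysis is a one-sample exact binomial test of the post-intervention rate and does not use the multilevel model.

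**The concern.** A random effect treats the units at that level as draws from a population and estimates their variance. Three clinics leave 2 degrees of freedom for that variance. The estimate is often zero. When it is, the model acts as if the clinics did not differ, and standard errors for quantities that vary between clinics become too small. Under the Bayesian option an estimate is always returned, but with three units the prior largely determines it. The clinics were also not sampled from a wider set, so the exchangeability behind a random effect has little to rest on.

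The search for significant moderators at clinic level has a related problem. Any clinic characteristic takes at most three distinct values, so it is nearly or wholly confounded with which clinic a patient attends.

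What is at stake is the explanatory analysis. Its results are meant to improve the implementation strategy, and the aims look ahead to a national randomised trial. A clinic variance of zero taken at face value, or a clinic feature reported as a driver of uptake, would misinform both.

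**Working it through.** The protocol states no intraclass correlation, variance component or power for the multilevel model, so there is no figure of its own to reproduce.

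**Inputs from the protocol:** 3 clinics; 365 enrolled, so 365/3 ≈ 122 per clinic; 317 analysed, so about 105 per clinic; anticipated post-intervention uptake 18.5%.

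**Assumption:** between-clinic SD of the logit, taken as 0.1, 0.2, 0.3 and 0.5.

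**1. Best-case precision of the clinic variance.** Suppose the clinic effects were normal and observed without error. The 95% limits, as multiples of the estimate, are df/χ²(0.975) and df/χ²(0.025), with df = 3 − 1 = 2.
- Lower: 2/7.378 = 0.27. Upper: 2/0.0506 = 39.5.
- On the SD scale: √0.27 = 0.52 to √39.5 = 6.28.
- With 30 clinics, for comparison, the SD limits would be 0.80 to 1.34.

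**2. How often the estimate is zero.** The sampling variance of one clinic's logit is s² = 1/(122 × 0.185 × 0.815) = 0.0544. The moment estimator is the variance of the three logits minus s², truncated at zero. With 2 df, the chance of a zero estimate is 1 − exp{−s²/(SD² + s²)}. For SD 0.3 this is 1 − exp(−0.0544/0.1444) = 0.31.

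**3. Coverage for the intercept.** The interval is the mean of the three logits ± 1.96 × √[(estimated variance + s²)/3], assessed by simulation with at least 200,000 replicates per setting.

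| Assumed SD | Zero estimate | Coverage of nominal 95% interval (intercept) |
|---|---|---|
| 0.1 | 57% | 95% |
| 0.2 | 44% | 92% |
| 0.3 | 31% | 88% |
| 0.5 | 16% | 84% |

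**4. Cross-check by maximum likelihood.** A random-intercept logistic model was fitted to 3 clinics of 105 patients (400 runs per setting, provider level ignored), with assumed intraclass correlations of 0.01, 0.02, 0.05 and 0.10. The clinic SD collapsed to about zero (below 0.05) in 67%, 58%, 33% and 24% of runs. The mean variance estimate was 58% to 74% of the true value. With 30 clinics of the same size the collapse rates were 15%, 1%, 0% and 0%.

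**5. Clinic-level moderators.** One clinic-level covariate leaves 3 − 2 = 1 df. The two-sided 5% critical value of t is 12.7, so the correlation across the three clinics must exceed 12.706/√(1 + 12.706²) = 0.997 in absolute value. Two covariates leave 3 − 3 = 0 df.

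**6. Patient-level moderators.** Simulation of 3 × 122 patients with a logit slope of 0.4 (2,000 runs per setting), forcing the clinic variance to zero in every run as a worst case:
- Covariate not clustered by clinic: slope coverage 95.0% at SD 0.3 and 94.9% at SD 0.5.
- 10% of the covariate's variance lying between clinics: 94.0% and 91.1%. With clinic as a fixed effect, about 95%.

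**The case against.** The strongest reply is that little is fixed here. The random effects are only to be considered, the article defers to a modelling text, and the SAP, where the choice between fixed and random clinic effects is often settled, is not shown. That is fair and lowers the weight of the point. Still, random effects for provider and clinic are the only structure named, next to an explicit search for significance at different levels.

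A reader might infer that the clinic variance cannot be estimated at all. The documents do not support that: with three clinics it is identifiable, but very imprecise and often zero. Nor is a test of one clinic-level moderator strictly impossible. It has 1 df and almost no power.

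A reader might also infer that every pooled estimate from the mixed model would carry wrong error bars. That does not follow. The coverage loss in step 3 concerns the intercept only, and overall uptake is to be estimated by an exact binomial interval, not from this model. The loss also disappears if the clinics barely differ (95% at SD 0.1). The moderators named in the third aim are patient-level, and step 6 shows nil to modest harm for them.

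Finally, the plan already repeats the descriptive and univariate analyses within each clinic, and the multilevel work serves to generate hypotheses. Both stand, and both bear on severity. Neither makes a three-unit random effect a good choice.

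**Conclusion.** The point holds in a limited form and is minor. With three clinics chosen by agreement, a random clinic effect would rest on a variance known at best to within 0.27 to 39.5 times its estimate, and clinic-level significance cannot be separated from clinic identity. The limits in step 1 and the degrees of freedom in step 5 need only the number of clinics and normality. The zero-estimate and coverage figures depend on assumed between-clinic SDs, equal clinic sizes and 18.5% uptake, and on leaving out the provider level.

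The primary test is unaffected. Patient-level moderators remain testable, with noticeable harm only if they differ between clinics and the clinics themselves differ substantially.

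**What to change.** In the pooled models, enter clinic as a fixed effect (two indicators) and keep the random effect for provider. Report clinic-level factors descriptively, without significance tests, and limit the search for significant mediators and moderators to the patient and provider levels. If a Bayesian clinic effect is kept, state an informative prior and a prior-sensitivity analysis.

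This is a change of wording. Data collection, recruitment and the primary analysis stay as they are. The cost is two parameters and the loss of formal generalisation to other clinics, which three clinics chosen by agreement could not support in any case.
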